**6. Number of subjects, allotment method**

6.1. Number of subjects

There will be 50 subjects when consumption is started—25 subjects taking the trial product and 25 subjects taking the placebo.

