**10. Schedule and examination content**

10.1. Trial schedule

(1) Preliminary examinations will be performed on candidate subjects who give consent. These will include a lifestyle questionnaire, interview, physical measurements, scientific measurements, ophthalmological examinations ( fundoscopy, vision test, refractometry, Schirmer’s test), and subjective evaluation of dry eyes (questionnaire).

(2) Fifty people who fit the objective of the trial will be selected based on the results of the preliminary examinations.

(3) The subjects who are selected will come to the clinic for pre-consumption examinations, which will include an interview, physical measurements, scientific measurements, ophthalmological examinations (functional vision test, break-up time of tear film (BUT), keratoconjunctival disorders), and subjective evaluation of dry eyes (questionnaire).

(4) After the pre-consumption examinations, the subjects will be given the allotted trial product so that they can begin taking it the following day. They will also begin making journal entries of details such as the time they consume the trial product.

(5) The subjects will come to the clinic during the fourth and eighth weeks of the trial to undergo physical measurements, scientific measurements, and ophthalmological examinations (functional vision test, BUT, keratoconjunctival disorders, Schirmer’s test).

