10.3. Survey and examination content

See the schedule above.

| Item | Content | |
| --- | --- | --- |
| Lifestyle questionnaire | Medical history, medical product and health food intake, allergies, smoking status, alcohol intake, subjective dry eye symptoms (DEQS), etc. | |
| Interview | Inquire about physical condition, check for adverse events | |
| Physical measurements | Height*^1^, weight, BMI | |
| Scientific examinations | Systolic blood pressure, diastolic blood pressure, heart rate, biochemical data(total protein, aspartate aminotransferase, alanine transaminase, lactate dehydrogenase, alkaline phosphatase, gamma-glutamyl transferase, urea nitrogen, creatine, uric acid, total cholesterol, low-density lipoprotein cholesterol, high-density lipoprotein cholesterol triglyceride, glucose, haemoglobin A1c) | |
|  | Fundoscopy | Examination by physician during interview*^1^ |
|  | Vision test | Measured using a visual examination device*^1^ |
|  | Functional vision test, | Examined using a functional optometer*^2^ |
|  | Refractometry | Examined using autorefractor keratometer*1 |
|  | BUT | Fluorescein BUT*^2^ |
|  | Keratoconjunctival disorder | Fluorescein stain test*^2^ |
|  | Schirmer’s test | *^3^ |

1. ^1^: Performed at preliminary examination only
2. ^2^: Performed starting with pre-consumption examination
3. ^3^: Performed at preliminary examination and eighth-week examination

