**15. Evaluation methods**

15.1 Evaluating efficacy

(1) Primary outcomes: subjective dry eye symptoms, BUT, keratoconjunctival disorders, Schirmer’s test

(2) Secondary outcomes: functional vision

(3) Efficacy evaluation methods

For each item, values before consumption and at each time point after consumption will be compared between the trial group and the placebo group using a 2-sample t-test. The amount of change from before consumption to each time point after consumption will be compared between the trial group and the placebo group using a 2-sample t-test. Values at each time point after consumption will be compared to values before consumption in each group using a 1-sample t-test.

For the baseline characteristics of patients with dry eye, Student’s t-test (p ≥ 0.05 by the F-test) will be used for comparison of age, and Pearson chi-square test will be used for categorical data of gender and dry eye diagnosis. Repeated measures analysis of variance followed by Tukey's honest significant difference (HSD) post hoc test will be used for analysis of dry eye symptoms. For the biochemical analysis, paired t-tests will be used for within-group comparisons and the F-test, followed by Student’s t-test (p≥0.05 by the F-test) will be used for between-group comparisons (placebo vs. RJ). A p-value of <0.05 was considered statistically significant. 16.2. Evaluating safety

(1) Outcomes

These are adverse events confirmed from interviews and journal entries (subjective symptoms), and abnormal variations in body weight and scientific examination values. For examination values, changes in items will be checked: body weight, systolic blood pressure, diastolic blood pressure, heart rate, and biochemical data.

(2) Evaluation methods

The number of adverse events and abnormal variations will be totaled to create a table. If the same adverse event occurs in the same subject multiple times, it will be treated as one event. To evaluate changes in examination values, measurements before consumption and at each time point after consumption will be compared using a 1-sample t-test. Figures will be displayed as mean ± standard deviation (or standard error). The significance level will be 2-sided 5%.

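### Efficacy is tested between groups by unranked t-tests on raw values and on changes, without baseline adjustment; one Week-8 ANCOVA per outcome would usually be more precise and give a single answer

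*Protocol*

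**What the plan says.** Protocol Section 15.1 (1) names four primary outcomes: "Primary outcomes: subjective dry eye symptoms, BUT, keratoconjunctival disorders, Schirmer’s test". Section 15.1 (3) then sets two between-group tests:

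- On raw values: "For each item, values before consumption and at each time point after consumption will be compared between the trial group and the placebo group", by a 2-sample t-test.
- On changes: "The amount of change from before consumption to each time point after consumption will be compared between the trial group and the placebo group", also by a 2-sample t-test.

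For one of the four primary outcomes there is a further method, a repeated measures ANOVA whose Tukey HSD "post hoc test will be used for analysis of dry eye symptoms". Post-baseline visits are at two times: "The subjects will come to the clinic during the fourth and eighth weeks of the trial" (Section 10.1). The threshold is p < 0.05, and the end of Section 16.2 calls it 2-sided. Section 15.1 names no covariate, no leading test and no deciding week.

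On size, Section 6.1 says "There will be 50 subjects when consumption is started", 25 per arm. Section 14.1 then limits the efficacy set to completers and removes those who took less than 80% of the product.

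**The concern.** The two t-tests put the same question to the same data and treat baseline in opposite ways. The raw-value test ignores it. The change test subtracts all of it, which amounts to a regression slope of 1. When the true slope lies between 0 and 1, neither makes the best use of a baseline measurement that the trial takes anyway. With 50 subjects, and fewer in the efficacy set, the lost precision counts.

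The two tests will also often disagree, and Section 15.1 has no rule for that case. The conclusion on an outcome could then depend on which result is put forward.

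**Working it through.** **Inputs from the protocol.** 25 per arm (Section 6.1); 2-sided 5% (Sections 15.1 and 16.2); follow-up at Weeks 4 and 8 (Section 10.1). The protocol gives no effect size, SD or power for its sample size, so there is no stated figure to reproduce.

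**Assumptions, not in the protocol.** Normal outcomes with equal variances; baseline–follow-up correlation r from 0.3 to 0.8; a true effect of 0.6 SD; all 25 per arm analysed.

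**Variance of the treatment contrast, relative to the raw-value test**

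- Raw value: 1
- Change: 2(1 − r)
- ANCOVA: 1 − r²

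Estimating the ANCOVA slope multiplies its variance by about 1 + 1/(N − 4) = 1 + 1/46 = 1.022 for N = 50. At r = 0.5 this gives 0.75 × 1.022 = 0.77, about 23% below either t-test.

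**Power for 0.6 SD.** The noncentrality is 0.6 / √(v × 2/25), where v is the relative variance. For the raw test this is 0.6 / 0.283 = 2.12 on 48 df, which gives 55%. For ANCOVA at r = 0.6 it is 0.6 / √(0.654 × 0.08) = 2.62 on 47 df, which gives 73%. ANCOVA power below includes the 1.022 factor; the variance columns do not.

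| r | Variance: raw | Change | ANCOVA | Power: raw | Change | ANCOVA |
|---|---|---|---|---|---|---|
| 0.3 | 1 | 1.40 | 0.91 | 55% | 42% | 58% |
| 0.5 | 1 | 1.00 | 0.75 | 55% | 55% | 66% |
| 0.6 | 1 | 0.80 | 0.64 | 55% | 64% | 73% |
| 0.7 | 1 | 0.60 | 0.51 | 55% | 77% | 82% |
| 0.8 | 1 | 0.40 | 0.36 | 55% | 91% | 93% |

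ANCOVA stops beating the raw test only where (1 − r²) × 1.022 reaches 1, at r of about 0.15 or below.

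**Chance imbalance.** Suppose the arms differ at baseline by D. Given D, the raw-value estimate is off by rD and the change estimate by −(1 − r)D. One standard error of D is √(2/25) = 0.28 SD. At r = 0.5 the raw estimate then moves by +0.14 SD and the change estimate by −0.14 SD, so the two are pushed apart.

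**Two answers (simulation, 25 per arm, 40,000 runs per setting, r from 0.3 to 0.8)**

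- No true effect, one time point: at least one of the raw and change tests is significant in about 9% of trials.
- No true effect, a single Week-8 ANCOVA: 4.9% to 5.1%.
- True effect of 0.6 SD: the two t-tests disagree on significance in 32% to 42% of trials.
- No true effect, both weeks: at least one of the four t-tests (2 tests × 2 weeks) on an outcome is significant in about 16%. ANCOVA at both weeks, with either one counting, still gives 9% to 10%.

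**Is the covariate available?** The schedule table ahead of Section 10 marks symptoms, BUT and keratoconjunctival disorder at the pre-consumption visit. For Schirmer's test the protocol disagrees with itself:

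- The schedule table marks all four visits.
- Section 10.1 (3) leaves it out of the pre-consumption examinations.
- Section 10.1 (5) lists it for Weeks 4 and 8.
- The Section 10.3 footnote says "Performed at preliminary examination and eighth-week examination".

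**The case against.** **The tests are valid.** In a randomized trial each t-test holds its 5% level. The shifts from imbalance are conditional on the imbalance seen and average out over randomization. This stands: the point is about efficiency and an unresolved choice. A reader might infer that either test is biased or invalid, and nothing in the protocol supports that.

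**The 9% is not the plan's error rate.** It applies only if an effect is claimed when either test succeeds, and the protocol states no such rule. This also stands. The figure is the cost of leaving the choice open, not of a decision rule that the protocol adopts.

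**A SAP may name the deciding test.** It may. But Section 15.1 itself prescribes the competing unadjusted tests and ranks none of them. A SAP that made ANCOVA decide would depart from the protocol, so the protocol wording needs the change.

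**The gain rests on unknown inputs.** True: r and the effect size are assumed. At r = 0.3 ANCOVA gains only 3 points on the raw test, and at r = 0.8 only 2 on the change test. But the protocol does not know which t-test would be the good one, and ANCOVA is at least as good as both from r = 0.2 up. The figures would also move with a smaller efficacy set, or if the staining result, whose scale Section 10.3 does not give, is far from normal.

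**ANCOVA does not cure multiplicity.** Correct. Applied at both weeks with either one counting, it has about the same error rate as the pair of t-tests at one week. It gives one answer per outcome only if one week decides and every competing between-group test steps down, the symptom ANOVA included.

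**Conclusion.** The point holds as a matter of precision and of an unranked choice. Section 15.1 (3) fixes two unadjusted between-group t-tests per item and time point, plus a third method for dry eye symptoms, and ranks none of them. Under equal variances and r between 0.3 and 0.8, ANCOVA has the smallest variance throughout. With 25 per group and an assumed 0.6 SD effect its power is 58% to 93%, against 55% for the raw test and 42% to 91% for the change test. Accepting either t-test would give about 9% error per outcome and time point.

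Two wider readings go too far. One is that ANCOVA would by itself control error for the trial: four primary outcomes without a rule across them remain. The other is that a pre-consumption covariate is assured for every primary outcome: for Schirmer's test the protocol contradicts itself. The change should be made, but the tests as written are not invalid.

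**What to change.** Amend Section 15.1 (3) as follows.

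1. Make one ANCOVA per outcome the deciding between-group analysis: Week-8 value on group, with the pre-consumption value as covariate. A mixed model for Weeks 4 and 8 with baseline and group-by-visit terms serves equally well if its Week-8 contrast is named as deciding.
2. State that it replaces both t-tests and, for dry eye symptoms, the repeated measures ANOVA with Tukey HSD.
3. Report the adjusted difference with its 95% confidence interval. Show raw values and changes descriptively.
4. For Schirmer's test, first reconcile the schedule table, Section 10.1 and the Section 10.3 footnote. Then use the resulting pre-treatment value as covariate, which is the preliminary value if no pre-consumption value exists. If there is no Week-4 value, use the Week-8 ANCOVA for this outcome.

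A rule across the four primary outcomes is a separate matter and still needed.

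The cost is a wording amendment with the sponsor's written consent and the ethics re-approval that Section 16.3 requires. No new measurements are needed, except that the reconciled schedule determines which Schirmer's values exist.

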**9. Protecting personal, and or other information**

The people involved in the trial will give full consideration to protecting a subject’s personal information and privacy when handling the consent forms and case report forms, and when publishing the data. Filling out case report forms, publishing articles, and submitting materials to regulatory authorities should be done in such a manner that a subject cannot be identified (for example assigning them identification numbers) to protect their privacy.

| Examination day | | Preliminary period |  | Consumption period (8 weeks) | | |
| --- | --- | --- | --- | --- | --- | --- |
|  | | Preliminary |  | Pre-consumption | Week 4 of consumption | Week 8 of consumption |
| Inclusion, allotment | |  | ○ |  |  |  |
| Lifestyle questionnaire | | ○ |  |  |  |  |
| Interview | | ○ |  | ○ | ○ | ○ |
| Physical measurements | Height | ○ |  |  |  |  |
|  | Weight | ○ |  | ○ | ○ | ○ |
| Scientific examinations | Systolic blood pressure | ○ |  | ○ | ○ | ○ |
|  | Diastolic blood pressure | ○ |  | ○ | ○ | ○ |
|  | Heart rate | ○ |  | ○ | ○ | ○ |
|  | Biochemical data |  |  | ○ |  | ○ |
|  | Fundoscopy | ○ |  |  |  |  |
|  | Vision test, refractometry | ○ |  |  |  |  |
|  | Functional visual acuityt |  |  | ○ | ○ | ○ |
|  | BUT | ○ |  | ○ | ○ | ○ |
|  | Keratoconjunctival disorder | ○ |  | ○ | ○ | ○ |
|  | Schirmer’s test | ○ |  | ○ | ○ | ○ |
| Subjective dry eye evaluation | DEQS | ○ |  | ○ | ○ | ○ |
| Consumption of trial product | |  |  | [figure not shown] | | |
| Journal records | |  |  | [figure not shown] | | |

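### None of the analyses named for DEQS, a primary outcome, adjusts for baseline; ANCOVA on scores already collected would be more precise at small cost

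*Protocol*

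**What the plan says.** Protocol Section 15.1 (1) lists four primary outcomes: "Primary outcomes: subjective dry eye symptoms, BUT, keratoconjunctival disorders, Schirmer’s test". Section 10.3 identifies the symptom measure as DEQS.

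The examination schedule table (printed at the end of Section 9) marks the row "Subjective dry eye evaluation | DEQS" at the preliminary visit, the pre-consumption visit, Week 4 and Week 8. Section 10.1 (1) and (3) agree with the table on the two early visits. So two DEQS scores exist for each subject before any product is taken.

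Section 15.1 (3) then names several analyses that apply to DEQS:

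- 2-sample t-tests between arms on the values at each visit.
- 2-sample t-tests between arms on change: "The amount of change from before consumption to each time point after consumption will be compared between the trial group and the placebo group".
- 1-sample t-tests within each arm.
- For this outcome in particular: "Repeated measures analysis of variance followed by Tukey's honest significant difference (HSD) post hoc test will be used for analysis of dry eye symptoms".

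No covariate appears in any of them. The section does not say which analysis decides, and the preliminary DEQS is not mentioned.

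**The concern.** A symptom score at one visit is a noisy measure. A raw Week 8 comparison discards what the baseline says about each subject. A change score uses the baseline with its coefficient fixed at 1, which over-corrects whenever the correlation between visits is below 1 and the variances are similar. ANCOVA estimates the coefficient from the data, so in large samples its variance is never above that of either t-test.

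With 25 subjects per arm at the start of consumption (Section 6.1), this lost precision matters for one of the four primary outcomes. The data that would recover it are already in the schedule.

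**Working it through.** **Inputs.** From the Protocol: 25 per arm, N = 50 (Section 6.1); two pre-consumption DEQS scores and a Week 8 score (schedule table); unadjusted tests, with significance at p < 0.05 (Section 15.1). The text at hand gives no DEQS standard deviation, target effect, power or between-visit correlation, so there is no figure of the plan's to reproduce. The correlation r is an assumption, shown from 0.3 to 0.9. An effect of 0.5 SD is assumed for illustration only.

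**Formulas.** Variance of the arm difference at Week 8, in units of SD² × 2/25, with equal variances and equal correlation r between any two visits:

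- Raw Week 8 value: 1
- Change score: 2(1 − r)
- ANCOVA, one baseline: (1 − r²) × 1.0217
- ANCOVA, two baselines: (1 − 2r²/(1 + r)) × 1.0444

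The multipliers are the finite-sample cost of k estimated covariates, 1 + k/(N − k − 3): 1 + 1/46 = 1.0217 and 1 + 2/45 = 1.0444.

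**Results under equal correlation.**

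| r | Change score | One baseline | Two baselines | One baseline vs change | Two baselines vs one |
|---|---|---|---|---|---|
| 0.3 | 1.400 | 0.930 | 0.900 | −34% | −3% |
| 0.5 | 1.000 | 0.766 | 0.696 | −23% | −9% |
| 0.7 | 0.600 | 0.521 | 0.442 | −13% | −15% |
| 0.9 | 0.200 | 0.194 | 0.154 | −3% | −21% |

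For the assumed 0.5 SD effect, power for change score, one baseline and two baselines is 42%, 52% and 56% at r = 0.5, and 63%, 69% and 76% at r = 0.7.

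**If the earlier score predicts less well.** In general the two-baseline residual variance is 1 − (r₁² + r₂² − 2r₁r₂ρ)/(1 − ρ²). Here r₁ and r₂ are the correlations of the pre-consumption and preliminary scores with Week 8, and ρ is the correlation between those two scores. Take a correlation of 0.6 between adjacent visits, decaying with distance: r₁ = 0.6, r₂ = 0.36, ρ = 0.6. The explained part is (0.36 + 0.1296 − 0.2592)/0.64 = 0.36, exactly what one baseline explains. The second covariate then only costs: 1.0444/1.0217 = 1.022, about 2.2% more variance. Simulated power (8,000 trials) was 49% for the change score, 58% with one baseline and 57% with two. The second covariate pays only if its partial correlation with the outcome exceeds about 0.15, from √(1 − 1.0217/1.0444).

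**If subjects were selected on the preliminary DEQS.** Section 10.1 (2) states: "Fifty people who fit the objective of the trial will be selected based on the results of the preliminary examinations". In simulation at r = 0.5, with only the upper half of preliminary scores enrolled, type I error stayed near 5%. Selection narrows the range of the preliminary score, so its contribution shrinks. Going from one baseline to two, the variance fell from 0.0582 to 0.0563 (about 3%), against 0.0621 to 0.0560 (about 10%) without selection.

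**The case against.** **The planned tests are valid.** A t-test on change is unbiased under randomisation, and covariate choice is often left to a SAP. The first part stands: this is lost precision, not an error. The second does not dispose of the point, because Section 15.1 (3) itself fixes the unadjusted tests.

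**The change score is not the only DEQS analysis.** A reader who stops at the change-score sentence might infer that it is. The Protocol does not support that, since it also names raw-value t-tests and a repeated measures ANOVA for dry eye symptoms. The visits entering that ANOVA are not listed, so it is not shown to exclude the preliminary score. As written, however, it carries no baseline covariate. If it used only the pre-consumption and Week 8 visits, its arm-by-visit test would be the same as the change-score test.

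**The second baseline is not free, and its gain is not assured.** A reader might infer that a score already collected gives precision at no cost. It uses a degree of freedom and can lose about 2%. Its gain depends on correlations, and on an interval between the two early visits, that the Protocol does not give. At r = 0.3 and 0.5 most of the gain comes from ANCOVA on one baseline.

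**The preliminary score may have been used for selection.** The schedule table places selection before allotment, so it acts on both arms alike and does not bias an adjusted comparison. It can reduce the second covariate's value, as shown above.

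**The pre-consumption score follows allotment in the table.** It still precedes the handing out of product (Section 10.1 (4)), so it is a sound covariate if blinding holds.

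**Fewer than 25 per arm may be analysed.** Section 14.1 restricts efficacy to completers with further exclusions, which makes the finite-sample cost slightly larger. The same rule means both DEQS scores should exist for every analysed subject.

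**Conclusion.** The point holds as an optional improvement in precision. No analysis in Section 15.1 (3) adjusts DEQS for baseline. Both ANCOVA forms had lower variance than the change score in every scenario computed.

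At assumed correlations of 0.5 to 0.7, one-baseline ANCOVA lowers variance by about 23% to 13% against the change score. The preliminary DEQS is the less certain increment: about 9% to 15% under equal correlation, about 3% with selection on it at r = 0.5, and none under decay.

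All these sizes rest on assumed correlations, equal variances and 25 analysed per arm. They do not show that the planned tests are biased or that the trial's conclusion would change.

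**What to change.** In Section 15.1 (3), name one deciding between-group analysis for DEQS: ANCOVA of the Week 8 score, with arm as factor and the pre-consumption and preliminary DEQS as two prespecified covariates. Week 8 matches the 8-week objective in Section 2. State that the raw-value and change-score t-tests and the repeated measures ANOVA with Tukey HSD are supportive, so that ANCOVA does not become one more competing test.

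Reconcile Section 10.1 (5), which omits the questionnaire at Weeks 4 and 8, with the schedule table, which includes it.

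Extend the approach to BUT, staining and Schirmer's test only after the schedule table, Section 10.1 and the footnotes in Section 10.3 are reconciled. The table marks all three at both early visits. The footnotes start BUT and staining at the pre-consumption visit and place Schirmer's test only at the preliminary and Week 8 visits.

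The cost is wording, one degree of freedom per covariate, and about 2% more variance if the preliminary score proves uninformative. No visit or measurement is added. The change should be fixed before the allocation table is opened (Section 6.2), and it needs ethics reapproval under Section 16.3 if the protocol has already been approved.

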**2. Trial objective**

The objective is to evaluate the effects of 8 continuous weeks of consumption of a food product containing royal jelly on the subjective assessment of dry eyes as well as ophthalmological examination results, in men and women aged between 20 and 60 years with dry eye symptoms, and to compare these effects to those of a placebo.

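### Before-after tests within each arm are listed as efficacy evaluation at the same 0.05 threshold as the between-arm tests, and nothing says that the between-arm comparison decides

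*Protocol*

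**What the plan says.** The objective in section 2 is to evaluate effects over 8 weeks "and to compare these effects to those of a placebo". The design in section 5 is randomized, double-blind and placebo-controlled.

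Section 15.1(3), on how efficacy is evaluated, sets out three tests for each item, in this order:

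1. Between arms, on values: "values before consumption and at each time point after consumption will be compared between the trial group and the placebo group using a 2-sample t-test".
2. Between arms, on change: "The amount of change from before consumption to each time point after consumption will be compared between the trial group and the placebo group", again by two-sample t-test.
3. Within each arm: "Values at each time point after consumption will be compared to values before consumption in each group using a 1-sample t-test".

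A second paragraph adds, for symptoms: "Repeated measures analysis of variance followed by Tukey's honest significant difference (HSD) post hoc test will be used for analysis of dry eye symptoms". It does not say whether the Tukey contrasts run between arms, within arms or both. That paragraph closes with the threshold: "A p-value of <0.05 was considered statistically significant". The safety subsection that follows gives the sidedness: "The significance level will be 2-sided 5" per cent.

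The protocol does not rank the three tests or name the one on which efficacy is concluded. The third is not marked as descriptive.

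**The concern.** A before-after test in one arm measures the sum of any product effect and everything else that changes over 8 weeks. Here that includes placebo response (one of the four primary outcomes is a symptom questionnaire), season (the trial is planned for May 2014 to March 2015) and repeated testing. These influences act on both arms, and only the contrast between arms removes them.

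The plan runs the before-after test in both arms. It therefore produces a pair of p-values that invites a comparison of significance: RJ significant, placebo not. That pattern is not a test of the difference between arms and is common when the difference is zero. If the between-arm test is null and the within-RJ test is significant, the protocol as written does not say which result is the efficacy finding.

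**Working it through.** The protocol gives no power, effect size, SD or expected placebo change, so there is no stated figure to reproduce. The check asks how often each test is significant when RJ does nothing.

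**Inputs**
- n = 25 per arm (section 6.1).
- Two-sided 5% level. The 0.05 threshold is in 15.1; the sidedness is taken from the safety subsection.
- True difference between RJ and placebo: zero, by construction.
- Common shift d in both arms, in SDs of the change score: **an assumption**, shown from 0 to 0.8.
- Change scores normal, with equal variance and independent between arms: assumed.

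**Within-arm test.** The one-sample t statistic on change has 24 degrees of freedom and noncentrality d × √25 = 5d. The critical value is 2.064. The probability of significance is p = P(|T| > 2.064). For d = 0.4, the noncentrality is 2.0 and p = 0.484.

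**RJ significant and placebo not.** The arms are independent and share the same shift, so the probability is p(1 − p). For d = 0.4: 0.484 × 0.516 = 0.250.

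**Between-arm test of change.** The shift d enters both means and cancels in their difference, so the rejection rate is the nominal 5% for any d. Simulation with 100,000 runs gave 4.9%, 4.9%, 4.9% and 5.0% at d = 0, 0.3, 0.5 and 0.8.

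| Assumed common shift (SD of change) | Within-RJ test significant | RJ significant, placebo not | Between-arm test of change |
|---|---|---|---|
| 0 | 5% | 5% | 5% |
| 0.2 | 16% | 13% | 5% |
| 0.3 | 30% | 21% | 5% |
| 0.4 | 48% | 25% | 5% |
| 0.5 | 67% | 22% | 5% |
| 0.8 | 97% | 3% | 5% |

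All rates are per outcome and per visit and count significance in either direction. At a shift of zero, half of the 5% is in the direction of improvement.

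The last-but-one column peaks at 25%, where p is close to one half, and falls again at large shifts because placebo then becomes significant too. At large shifts the hazard is the within-RJ result read alone.

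**Fewer analysed.** Section 14.1 restricts the efficacy set to compliant completers. If 20 per arm remained (an assumption), the within-RJ test would be significant in 25%, 56% and 92% of trials at shifts of 0.3, 0.5 and 0.8, and RJ alone in 19%, 25% and 7%.

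**Regression to the mean.** Section 10.1(2) says "Fifty people who fit the objective of the trial will be selected based on the results of the preliminary examinations", so selection on poor screening values is possible. For outcomes measured again before consumption, part of any regression has happened by baseline. The route is clearest for Schirmer's test if its baseline is the screening value. Note 3 to the table in 10.3 implies this by placing the test at the preliminary and week 8 visits only. The examination schedule at the end of section 9 contradicts that note by marking it at all four visits, and 10.1(5) includes it at week 4. No cut-off or ranking for selection is given, so no percentage is attached to this route.

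**The case against.** The strongest reply is that the right contrast is already planned, and planned first. Two between-arm tests precede the within-arm sentence, and the objective and design both point to placebo. Nowhere does the protocol say that efficacy may be claimed from a within-arm result. The ranking of analyses is also often left to an analysis plan, which is not at hand.

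Much of this stands. A reader might infer that the protocol lacks a proper placebo comparison, or that it adopts RJ significant with placebo not as its criterion for success. The text supports neither. What remains is that the protocol itself places the within-arm tests under efficacy evaluation, gives one threshold for the section and names no deciding test. That is a stated choice, not an omission left for later.

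A second reply is that the size depends wholly on an assumed shift. That is correct. Shifts of 0.3 to 0.5 SD lie around the peak for RJ alone being significant, so 21% to 25% is the top of the range and not a typical value. At 0 and 0.8 SD the figure is 5% and 3%.

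Third, a reader might infer that selection of symptomatic people makes large false within-arm improvements certain through regression to the mean. The documents do not support a figure: the Schirmer schedule is contradictory and the strength of selection is unstated.

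Finally, a 95% interval that excludes zero carries the same information as the one-sample t-test. The gain therefore comes from the rule about what decides and from the descriptive label, not from swapping a p-value for an interval.

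**Conclusion.** The point holds as a defect of interpretation that should be fixed before unblinding. Randomization, blinding, data collection and the between-arm tests are unaffected, so it does not threaten the validity of the trial.

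If an efficacy claim rested on the within-RJ test, its false-positive rate per outcome and visit would rise from 5% with no common shift to 30% at 0.3 SD and 67% at 0.5 SD. If it rested on RJ being significant and placebo not, the rate would be 3% to 25% across the range shown. If it rests on the between-arm change, the rate is 5% throughout. These figures assume 25 analysed per arm, normal change scores and a common shift that the protocol does not quantify. The logical point, that a within-arm test does not address the objective, needs none of those assumptions.

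The within-group tests planned for safety values and biochemistry are a separate matter and are not part of this point.

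**What to change.** In section 15.1(3):

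1. State that efficacy is concluded only from the between-arm difference in change from baseline.
2. Remove the within-arm one-sample t-tests from the efficacy methods. Report mean change in each arm with a 95% confidence interval, labelled as description only.
3. Say which contrasts the repeated-measures ANOVA and Tukey procedure will test for symptoms, and apply the same rule to any that are within an arm.

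Separately, reconcile note 3 in 10.3 with the examination schedule and 10.1, so that the baseline for Schirmer's test is unambiguous.

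Points 1 to 3 need a few sentences and no extra subjects, visits or data. The price is that a nominally significant within-arm result can no longer be claimed as efficacy.
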